### Objectives

The following objectives will be addressed:

1. To determine the incidence of missed or delayed diagnoses with either imaging scheme,

2. To define the diagnostic accuracy of either MDCT protocol, based on the synopsis of clinical, imaging, and interventional information gathered until discharge,

3. To evaluate patients’ safety with either protocol,

4. To determine the exposure to radiation and the LAR of cancer with either approach,

5. To evaluate subjective and objective measures of image quality.

### Setting

This is a single-centre non-interventional study using approved and established MDCT imaging protocols for severely injured patients. The study compares a cohort of subjects receiving the standard of care, i.e., single-pass, whole-body 128-MDCT with regular image acquisition and processing, with a subsequent cohort receiving single-pass, whole-body 128-MDCT with a radiation-dose reducing iterative reconstruction method (iDose). Table 1 summarizes key items of both protocols. Figure 1 shows the anticipated study flow.

**Table 1 T1:** Key scanning parameters in the experimental and the control group

	**Standard dose**	**Low dose**
	**128-row MDCT pan-scan**	**128-row MDCT pan-scan + iDose**
Detector z coverage, mm	40	40
kVp	120	120
Exposure, mAs	180	90
iDose Level	off	4 (6)
Recon filter	B	B (C)
CTDI, mGy	11.9	5.9

**Figure 1 F1:**
[figure not shown]
Anticipated study flow.

### Primary outcome

Delayed diagnoses comprise pathological anatomic and / or physiologic findings which demand clinical awareness, or, in case of therapeutically relevant pathological results, should prompt immediate therapeutic action.

We will estimate the incidence of delayed diagnoses based on a synopsis of all subsequent clinical, imaging, intra-operative, and autopsy findings until discharge. We will further distinguish between clinically relevant and all diagnoses. Relevant diagnoses are defined as severe injuries suiting an Abbreviated Injury Scale [AIS] score ≥3 and/or injuries demanding surgical and/or trans-vascular intervention. Non-traumatic incidental findings like tumours or tumour-like lesions demanding specific work-up and/or treatment will be recorded in an exploratory attempt.

### Secondary outcomes

#### Accuracy

Accuracy (or diagnostic efficacy) is a key indicator of performance of an imaging technology. In pan-CT for trauma, there are five variables contributing to overall accuracy:

1. The general technical capability of CT technology to depict a certain pathology (resolution)

2. Trauma-associated, acutely impaired physiological parameters (e.g., hypotension, haemorrhagic shock, centralized circulation) which hamper organ perfusion and/or vessel contrast

3. The interval needed for tissue contusions and hematomas to demark or expand

4. Interpretation of images by the radiologist on call

5. The severity and/or therapeutic consequences of findings

In addition to the incidence of delayed diagnoses, we will compute standard indicators of diagnostic test accuracy (i.e., sensitivity, specificity, positive and negative predictive values, areas under the ROC). Different models will be created for various endpoints (e.g., all missed injuries, therapeutically relevant findings, and others).

#### Safety

Any situation in which the individual patient’s safety is assumed to be compromised will be recorded and evaluated in a cumulative fashion. Safety-relevant events will be entered in the local Critical Incident Reporting System (CIRS), hosted by the Medical Council (Ärztekammer) of Berlin, Germany. Since this is an observational study, we will use common definitions of adverse events (AE), serious adverse events (SAE), and Suspected Unexpected Serious Adverse Reactions (SUSAR), as outlined in ICH Topic E2B (Clinical Safety Data Management: Data Elements for Transmission of Individual Case Safety Reports), and most recently in the amended and updated DIN-ISO 14155 guideline, but do not implement a regular reporting procedure.

#### Radiation dose and estimated LAR of cancer

Dose calculation includes

- CTDI_vol_, scan length, DLP as reported by the scanner (dose report page in PACS), and verified by software CT-Expo, if values are ambiguous or information is missing

- Effective dose (in mSv) calculated by CT-Expo from documented parameters, based on most recent ICRP recommendations (modified tissue-weighting factors)

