Modern 64-, 128- and 256-row MDCT scanners are regarded to produce lower dose indexes (CTDI_vol_) than earlier generation single- or 4-row hardware. However, Harrieder et al. recently demonstrated in a retrospective study that, because of enhanced scan lengths, the dose-length-product (DLP) may remain similar or even increase with modern hardware [27]. The authors, however, provided little information on patient demographics (e.g., BMI, ISS) and did not only compare different multi-detector-row technologies but also scanners made by different manufacturers. A comparison of 64-row scanners of four leading companies suggested highest patient mean effective doses (in mSv) produced by the GE LightSpeed VCT (12.7 ± 2.6), followed by the Toshiba Aquilion (11.1 ± 3.3), Philips Brilliance (9.5 ± 0.4) and Siemens Somatom (9.1 ± 1.1) [28].

So-called adaptive statistical iterative algorithms (ASIR), derived from a Bayesian framework, incorporate i. random fluctuations in sinogram measurements [29], ii. non-ideality, iii. different degrees of data credibility, iv. *a priori* information about the distribution of the image space, and other previously unconsidered variables to enhance resolution and reduce artefacts and noise [30].

Distinct technologies like Veo (Model Based Image Reconstruction, GE Healthcare) or IRIS (Iterative Reconstruction in Image Space, Siemens) received FDA approval [31].

Apart from phantom studies and smaller case series, there is currently sparse evidence from head-to-head studies about the effect of ASIR technology on objective and subjective image quality, and exposure to radiation. Exemplarily, Prakash et al. from Boston showed in a cohort of 222 patients who had previously undergone abdominal CT with filtered back projection (FBP) technology and were scheduled for follow-up ASIR scan that CTDL_vol_ and DLP were markedly reduced without compromising image quality [32]. The Prakash group showed similar results in chest CT [33,34]. Other investigators reported similar dose reductions with similar image quality in CT portovenography [35], cerebral CT [36], and abdomino-pelvic CT scans [37].

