### Recruitment and documentation

Patients will be recruited under routine clinical care conditions, and documentation will mainly comprise data collected for administrative issues or routinely entered in the electronic patient chart. Also, all radiological images will be stored in a PACS for later processing and evaluation.

We will record all patients participating in this study immediately after they underwent the MDCT scan. Informed consent will be gathered by relatives or the next of kin, or individual patients as soon as they are able to consent in using their data for scientific purposes.

This study focuses on delayed and missed injuries, and the accuracy of the primary MDCT scan. Thus, it needs a diagnostic reference or gold standard.

The probably best reference method to which initial MDCT findings can be compared is the clinical and radiological follow-up. If the initial MDCT misses injuries in severely injured patients, it is very likely they will be detected during hospital stay (the same holds true for suspected pathological findings which cannot be confirmed or verified on follow-up imaging).

This study will employ a synopsis of all clinical (including intra-operative) and radiological findings collected until discharge as the diagnostic reference standard. All these items will be traced from routinely available information.

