### Sample size considerations and calculations

The sample size is calculated to guarantee a certain precision of a range of estimates, not to achieve a certain power to detect an *a priori* defined effect size.

With 500 eligible cases in either cohort, this study fulfils the following prerequisites:

1. 95% confidence intervals of both risk and mean differences must not exceed the point estimate by more than 5% in either direction

2. multivariate modelling must be possible for five independent covariates (respecting Harrell’s rule)

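### The dose items listed for Objective 4 describe a scan, so the study can compare index-scan exposure and cancer risk but not net in-hospital exposure if low-dose imaging leads to more repeat CT

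*Protocol article*

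**What the plan says.** The fourth objective (Objectives) is: "To determine the exposure to radiation and the LAR of cancer with either approach". The abstract also names radiation exposure among the main outcomes.

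Under Secondary outcomes, Radiation dose and estimated LAR of cancer, two items are listed. The first is CTDIvol, "scan length, DLP as reported by the scanner (dose report page in PACS"), with a software check where values are ambiguous or missing. The second is "Effective dose (in mSv) calculated by CT-Expo from documented parameters, based on most recent ICRP recommendations (modified tissue-weighting factors"). The list is introduced by the word *includes*. It names no dose from later scans and does not say how doses are added up within a patient.

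Table 1 (Setting) gives both protocols at 120 kVp, with the rows "Exposure, mAs 180 90" and "CTDI, mGy 11.9 5.9" (standard dose first, low dose second).

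The diagnostic side has a longer horizon. Primary outcome counts delayed diagnoses from everything found up to discharge, and Recruitment and documentation uses a "synopsis of all clinical (including intra-operative) and radiological findings collected until discharge as the diagnostic reference standard". That section also says that all radiological images are kept in the PACS.

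**The concern.** The two sides of the comparison cover different periods. Harm, meaning a delayed or missed diagnosis, is followed to discharge. Benefit, meaning lower exposure, is described only by quantities that belong to a scan.

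The nominal dose contrast of the index scan is known before the first patient is enrolled. What is not known is whether images taken at half the exposure are followed by more CT during the stay, because a finding is uncertain or an injury is suspected later. Recruitment and documentation expects follow-up imaging to reveal missed injuries and to settle suspected ones. Such scans would feed the delayed-diagnosis and accuracy outcomes, but their dose is not named as part of exposure or LAR.

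The Discussion presents the study as possible evidence for choosing between the two approaches. If the low-dose cohort needs more repeat CT, a reader who takes the index-scan saving as the patient's saving would overrate the benefit being set against missed injuries.

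**Working it through.** **Inputs from the article.** Table 1: 120 kVp in both protocols, 180 v 90 mAs, CTDI 11.9 v 5.9 mGy. Sample size considerations: "With 500 eligible cases in either cohort". The repeat-CT rate, the length and dose of repeat scans, and the between-patient variation in dose are not given. Where they are needed below, they are assumptions.

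**1. Is the CTDI contrast set by the protocol?** At fixed kVp, CTDI is proportional to mAs.
- Expected low-dose CTDI: 11.9 × 90/180 = 5.95 mGy, against 5.9 printed (0.8% apart). Table 1 is consistent with itself.
- CTDI ratio: 5.9/11.9 = 0.496. Index saving: (11.9 − 5.9)/11.9 = 0.504, or 50%.

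**2. How far could scan length undo it?** DLP = CTDIvol × scan length. To cancel the saving, mean length in the low-dose cohort would have to be 11.9/5.9 = 2.02 times that in the standard cohort. DLP is therefore not fixed by the settings, but a ratio far from one half would need a large difference in length.

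**3. How precisely would the index contrast be measured?** Assume log-normal doses with coefficient of variation CV. Then s = √ln(1 + CV²), SE = s × √(2/500), and the 95% CI is 0.496 × exp(±1.96 SE).
- CV 10%: 0.490 to 0.502.
- CV 50%: 0.468 to 0.526.

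Either way, the result would mainly confirm a halving that is already expected.

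**4. What would cancel the saving?** Let e be the extra later scans per low-dose patient, each of full pan-scan length. The saving is expressed relative to one standard index scan.

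| Extra scans e | Net saving, extras at 11.9 mGy: 0.504 − e | Net saving, extras at 5.9 mGy: 0.504 − 0.496e |
|---|---|---|
| 0.05 | 45% | 48% |
| 0.10 | 40% | 45% |
| 0.20 | 30% | 41% |
| 0.30 | 20% | 36% |
| Break-even | e = 0.504 | e = 1.02 |

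A repeat scan of one body region counts as less than one equivalent, so more such scans would be needed to reach break-even.

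**5. What would the cumulative ratio look like?** Let F be later CT dose common to both cohorts, in units of one standard pan-scan, and let e now be extra standard-dose equivalents in the low-dose cohort. Cumulative ratio = (0.496 + F + e)/(1 + F).

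| F | e = 0 | e = 0.25 |
|---|---|---|
| 0.25 | 0.60 | 0.80 |
| 0.5 | 0.66 | 0.83 |
| 1 | 0.75 | 0.87 |
| 2 | 0.83 | 0.92 |

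Even with no extra scans, shared later imaging dilutes the relative contrast. The absolute saving still vanishes at e = 0.504 whatever F is. If later CT in the second cohort were also done at the low dose, with no extra scans, the ratio would stay at 0.496. The article does not say which of these applies, and the listed dose items would not tell them apart.

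**The case against.** The strongest reply is that silence in a condensed article is being read as a rule. The dose list is open-ended, does not exclude later CT, and names the quantities from which a cumulative dose would be built. Which scans count, and how effective dose becomes LAR, may be set out in the full protocol or analysis plan. Objective 4 speaks of exposure with either approach, and the approaches are two protocols for one primary scan. It promises neither total nor cumulative exposure. This stands: no stated objective is contradicted, and the missing LAR algorithm is not a finding.

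Two stronger readings are tempting, and the article supports neither.
- A reader might infer that the whole dose outcome is fixed by the scanner settings. Only nominal CTDI is. The Background itself reports that "because of enhanced scan lengths, the dose-length-product (DLP) may remain similar or even increase with modern hardware", and effective dose also depends on patient and anatomical factors. Measuring achieved dose therefore has some value.
- A reader might infer that the outcome cannot show whether cancer risk falls. Effective dose is an input to LAR, so risk attributable to the index scan can be compared. Only risk based on net in-hospital exposure is out of reach.

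It is also fair to say that cumulative dose should not replace index dose. The cohorts are consecutive and not randomised, and later CT depends on injury severity, survival, length of stay and changes in practice. The index-scan comparison is the cleaner one. Finally, the repeat rates and the full scan length used above are assumptions, and nothing in the article says that low-dose imaging does lead to more CT.

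What remains is that the items actually stated describe scans, while the harm outcomes run to discharge.

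**Conclusion.** The point holds in a limited form. The listed dose items support a comparison of index-scan exposure and index-scan LAR, with a CTDI ratio of 0.496 that Table 1 largely presets. They do not, as described, support a conclusion about net in-hospital exposure or the LAR based on it.

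The gap is bounded by the break-even figure: about 0.50 extra standard-dose, full-length scan equivalents per low-dose patient would cancel the 50% saving. This assumes equal scan length and the same effective dose per unit of CTDI × length in both cohorts. Whether the true number of extra scans is near zero or near that bound cannot be judged from the article.

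This is a worthwhile and inexpensive addition to a secondary outcome. It is not an error in the primary outcome or in the index-dose comparison.

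**What to change.** Keep the index-scan dose and its LAR as the comparison of the two protocols. State that they refer to the index scan. Beside them, specify:

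- cumulative CT effective dose per patient from admission to discharge, covering all CT;
- the LAR based on that cumulative dose;
- the number of repeat CTs per patient, by cohort.

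Compare these with the regression adjustment already planned, with injury severity among the covariates. Take account of survival and length of stay, since death or early discharge shortens the time in which later CT can occur. Length of stay may itself be affected by a delayed diagnosis, so showing results with and without that adjustment is safer than relying on one model.

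**Cost.** Dose-report pages for later scans must be read from the PACS, where the images are already stored. No patient procedure changes. The cumulative contrast will probably be smaller in relative terms, more variable and more open to confounding than the index-scan contrast. It should be reported as a complement with that caution.

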#### Subjective image quality

Numerous approaches have been proposed to quantify the quality of CT images in the transversal plane, and to generate resource-intensive but clinically required coronal, sagittal, and 3-D reconstruction views.

Basically, there are two different, still complementary concepts to quantify image quality:

1. Subjective evaluation of quality, ideally assessed by two or more independent expert raters in a random, blinded (towards the underlying processing algorithm) fashion, using pre-defined body areas and instruments or scales

2. Objective evaluation, using physical parameters like contrast/signal, noise, and the ratio of both

There is currently no consensus or a reproducible pattern of criteria available to distinguish “good” or “diagnostic” from “unacceptable” or “un-diagnostic” images. In 1999, the European Commission had summarized quality criteria in a guideline (EUR 16262 EN, http://w3.tue.nl/fileadmin/sbd/Documenten/Leergang/BSM/European_Guidelines_Quality_Criteria_Computed_Tomography_Eur_16252.pdf) which had lastly been updated in 2004 (http://www.msct.eu/CT_Quality_Criteria.htm).

Latest updates on the web-platform of the Imaging Performance Assessment of CT Scanners (IMPACT, http://www.impactscan.org/) working group have been made in 2010.

From a statistical point of view, 3- and 5-point ordinal scales have the disadvantage of a non-normal / non-parametric distribution. Although frequently used, the central measure of these scales is not the parametric mean but the geometric mean or median. For sample size calculations and full-scale variance, a visual analogue scale is the better option to determine image quality.

To overcome the limitations with established rating scales, wet set up a pilot study using 2 x 20 sets of images from patients with multiple trauma. The control set consisted of images obtained by a 64-row MDCT scanner (Brilliance 64, Philips, Germany), with scanning parameters published elsewhere [18]. The experimental set comprised images obtained by the 128-row MDCT (Ingenuity Core 128, Philips) scanner to be used in the planned project.

Two independent radiologists blinded to the scanner generation and protocol rated image quality on a 100-mm visual analogue scale, focusing on lung, bone, vessel, fluid/fat and organ tissue contrast.

The arithmetic mean of both raters with the pooled standard deviation s, calculated as

(1)$$s=\sqrt{\frac{\left(n_{1}–1\right)\;S_{1}^{2}+\left(n_{2}–1\right)\;S_{2}^{2}}{n_{1}+n_{2}–2}}$$

was used for quantitative assessment of differences between groups. Here, n_1_ and n_2_ are the number patients / images assessed by rater 1 and 2, and S_1_ and S_2_ are the standard deviations of means.

There were no marked differences in quality ratings between images obtained by either method (Table 2). According to the observed standard deviations, a 1 ± 4 mm difference on the 100-mm VAS appears as the minimally detectable difference between both imaging protocols.

**Table 2 T2:** Summary of the results of the pilot study

**Tissue**	**Pooled mean (SD)**		**Mean difference (95% ****CI)**
	**64-row**	**128-row**	
Lung	93.90 (1.89)	93.30 (2.03)	0.60 (-0.66 to 1.86)
Bone	93.28 (2.32)	92.15 (3.63)	1.13 (-0.82 to 3.08)
Vessel	91.60 (3.31)	89.90 (4.84)	1.70 (-0.95 to 4.35)
Organ	89.60 (3.92)	85.98 (7.87)	3.62 (-0.36 to 7.60)
Fluid/Fat	92.98 (3.39)	90.78 (4.43)	2.20 (-0.33 to 4.73)

A 100-mm VAS was used for subjective image quality assessment.

#### Objective image quality

Contrast and noise, and the ratio of both, are amongst the most influential indices to describe the objective quality of CT images.

The contrast-to-noise ratio (CNR) is defined as

(2)$$\mathrm{CNR}=\frac{\left|s_{1}–s_{2}\right|}{\sqrt{\frac{\sigma_{1}^{2}+\sigma_{2}^{2}}{2}}}$$

where S_1_ = mean CT number (in HU) in region of interest 1 (ROI_1_) 1, S_2_ = mean HU in ROI_2_, σ_1_ = mean SD of the mean HU in ROI_1_, and σ_2_ mean SD of the mean HU in ROI_2_

Standard ROIs of similar size and position are placed in prominent anatomical structures such as the aorta, liver, other solid organs and spinal muscles. If metal implants are present, then ROIs shall also be placed in the vicinity.

### Patients

This study will include a representative German and European trauma population, meaning that eligible patients had

1. sustained blunt major trauma by a car crash or fall from a height

2. been resuscitated on scene by a multi-professional team of paramedics and emergency physicians, including sedation / general anaesthesia and airway management by oro-tracheal intubation

Thus, the target sample unavoidably includes incompetent (i.e., unconscious and ventilated, probably hemodynamically unstable) patients.

An injury is an unpredictable event that may occur in all age groups, and regardless of other medical conditions. Some patients may also not have reached the legal age of consent at the time of injury.

Patients with the following characteristics are eligible to be enrolled in the planned study:

1. Male and female patients of all ages

2. Suspected or already proven blunt multiple trauma, as indicated by the presence of injuries to ≥2 body regions which, alone or in combination, are life-threatening, or an ISS ≥16

3. *Indication for primary, single-pass whole-body CT by judgment of the trauma leader in charge* and according to red flag criteria outlined in the German Trauma Association’s clinical practice guideline on the management of multiple trauma [45]:

any injury mechanism exposing patients to a high risk of multiple trauma (i.e., road traffic crash with presumed high-energy trauma like extrication or death of a car occupant, pedestrian struck by a vehicle, fall from height)

need for technical rescue

impaired physical or physiological status (i.e., unconsciousness, intubation and ventilation, obvious signs of injury like bruises, haematoma, open wounds or fractures, hemodynamic instability)

suspicion of severe trauma confirmed by paramedics and/or emergency doctors on scene

This study evaluates routine clinical practice and consecutive patients. Since this includes only subjects who undergo primary, single-pass MDCT for clinical indication, those

1. considered unsuitable for CT for any reason (e.g., need for immediate life-saving thoracotomy, laparotomy, or cranial trepanation)

2. with futile resuscitation and / or CPR efforts

3. declared dead on arrival will be missed by this study.

### Recruitment and documentation

Patients will be recruited under routine clinical care conditions, and documentation will mainly comprise data collected for administrative issues or routinely entered in the electronic patient chart. Also, all radiological images will be stored in a PACS for later processing and evaluation.

We will record all patients participating in this study immediately after they underwent the MDCT scan. Informed consent will be gathered by relatives or the next of kin, or individual patients as soon as they are able to consent in using their data for scientific purposes.

This study focuses on delayed and missed injuries, and the accuracy of the primary MDCT scan. Thus, it needs a diagnostic reference or gold standard.

The probably best reference method to which initial MDCT findings can be compared is the clinical and radiological follow-up. If the initial MDCT misses injuries in severely injured patients, it is very likely they will be detected during hospital stay (the same holds true for suspected pathological findings which cannot be confirmed or verified on follow-up imaging).

This study will employ a synopsis of all clinical (including intra-operative) and radiological findings collected until discharge as the diagnostic reference standard. All these items will be traced from routinely available information.

